**Methods:**

A multidisciplinary team of endocrinologists, experts in medical education, and programmers, was assembled for the design and development of InsuOnline. Currently, we are conducting usability and playability tests, with PCPs and medical students playing the game on a desktop computer. Adjustments will be made based on these results. An unblinded randomized controlled trial with PCPs who work in the city of Londrina, Brazil, will be conducted to assess the educational validity of InsuOnline on the Web. In this trial, 64 PCPs will play InsuOnline, and 64 PCPs will undergo traditional instructional activities (lecture and group discussion). Knowledge on how to initiate and adjust insulin will be assessed by a Web-based multiple choice questionnaire, and attitudes regarding diabetes/insulin will be assessed by Diabetes Attitude Scale 3 at 3 time points—before, immediately after, and 6 months after the intervention. Subjects´ general impressions on the interventions will be assessed by a questionnaire. Software logs will be reviewed.

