We will evaluate subjects´ knowledge on insulin therapy using a Web-based questionnaire, containing 10-20 multiple choice questions. The questions will be clinical vignettes of diabetic patients who require initiation and/or adjustment of insulin. For each question, the participant should choose the best option for achieving a better glycemic control, according to current guidelines [1,29-31. Questions regarding insulin therapy will be selected from the American Diabetes Association Self-Assessment Program, Module 2 (Pharmacological Treatment of Hyperglycemia) [35], translated to Portuguese, and adapted to be compatible with the game´s clinical scenarios and learning objectives. Participants´ attitudes regarding diabetes will also be assessed, by the application of Web-based Diabetes Attitudes Scale, version 3 (DAS-3) [36]. The questionnaire and the DAS-3 will be answered by the participants at 3 time points: before the intervention (pre-test), immediately after the intervention (after-test), and 6 months after the intervention (late-test). The average number of right answers will be presented and compared in the different time points within each group (intragroup) using analysis of variance (ANOVA), and between the 2 groups at each time point (intergroup) using Student´s *t* test. A bicaudal significance level of 0.05 will be adopted. Data analysis will be done by intention-to-treat, with last observation carried forward, which means that all randomized participants´ data will be included in the final analysis.

The participants will be asked a few Likert-scale and free text questions at the end of each intervention to assess their general impressions about the intervention (mostly to assess if it was pleasant or enjoyable). Software-recorded data on player´s usage of the game will be analyzed to assess the number of logins, time spent on the game, etc. For the participants in Group A that do not finish the game, the reasons for early withdrawal will be collected by an online questionnaire. We will contact (by phone or email) the participants who do not eventually fulfill the questionnaires at least twice.

In order to detect a minimum standard deviation of 0.5 on the average of right answers with 80% of statistical power at 5% of significance level, we will need to include 128 subjects in our study (64 in each group). We will enroll 160 subjects (80 in each group), in order to compensate for an expected 25% dropout rate.

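### The enrolment of 160 offsets a 20% dropout, not the stated 25%; at 25%, 60 per group have observed outcomes and power among them is 77.5%, not 80%

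*Protocol article*

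**What the plan says.** All the figures stand in the Educational Efficacy Assessment section of the Protocol article.

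- **Target:** "In order to detect a minimum standard deviation of 0.5 on the average of right answers with 80% of statistical power", at the 5% level.
- **Required size:** "we will need to include 128 subjects in our study (64 in each group").
- **Enrolment:** "We will enroll 160 subjects (80 in each group), in order to compensate for an expected 25% dropout rate".
- **Test:** the groups are compared "between the 2 groups at each time point (intergroup) using Student´s" t test, and "A bicaudal significance level of 0.05 will be adopted".
- **Dropouts in the analysis:** "Data analysis will be done by intention-to-treat, with last observation carried forward", so every randomised participant is analysed.

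The Methods paragraph of the abstract gives only the smaller number: "64 PCPs will play InsuOnline, and 64 PCPs will undergo traditional instructional activities (lecture and group discussion").

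**The concern.** Required number, enrolled number and expected dropout are tied by one equation: enrolled × (1 − dropout) = required. The three stated values do not satisfy it. The margin appears to have been added as 25% of the required number, whereas a dropout rate is a fraction of those enrolled.

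What is at stake is the accuracy of a stated design property. The text tells the reader that the dropout margin protects 80% power at the expected loss, and on its own figures it does not. The test and the comparison made are unaffected.

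**Working it through.** **Inputs, all from Educational Efficacy Assessment.** Difference 0.5 SD; two-sided α = 0.05; power 80%; equal groups; Student's t test; 128 required; 160 enrolled; 25% dropout. The article's phrase about a minimum standard deviation of 0.5 is read as a difference of 0.5 SD. Step 1 supports that reading.

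**Step 1: reproduce the required number.** For a two-sample t test with n per group, the noncentrality parameter is d × √(n/2) on 2n − 2 degrees of freedom.

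- n = 63: power 79.5%.
- n = 64: 0.5 × √32 = 2.83 on 126 degrees of freedom; power 80.1%.

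The smallest adequate size is therefore 64 per group, 128 in total, as stated. A one-sided test would need 50 per group and does not fit. This part of the plan is correct.

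**Step 2: reproduce the enrolment.**

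- 128 × (1 + 0.25) = 160, the stated figure.
- 128 / (1 − 0.25) = 170.7, so 171 in total. Per group, 64 / 0.75 = 85.3, so 86 (172 in total).

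The stated figure comes from the multiplication. The division, which is the one that offsets a 25% loss, gives 11 to 12 more.

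**Step 3: what 160 delivers.**

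- At 25% dropout: 160 × 0.75 = 120 observed, 60 per group; 128 − 120 = 8 short.
- Dropout that 160 does offset: 1 − 128/160 = 20%.

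**Step 4: power if dropouts are lost.** At n = 60 the noncentrality parameter is 0.5 × √30 = 2.74 on 118 degrees of freedom.

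| Observed per group | Power at 0.5 SD (t test) | Normal approximation |
|---|---|---|
| 64 | 80.1% | 80.7% |
| 60 | 77.5% | 78.2% |

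The difference detectable with 80% power at 60 per group is 0.516 SD, against 0.50 SD at 64.

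**Step 5: power if all 160 are analysed with carried-forward values.** The article does not say how much of the effect a carried-forward score retains. Assume that the 25% who drop out keep a fraction f of the 0.5 SD effect and that the SD is unchanged. The mean difference is then 0.5 × (0.75 + 0.25f), tested with 80 per group.

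| f | Difference (SD) | Power |
|---|---|---|
| 0 (only the pre-test carried forward) | 0.375 | 65% |
| 0.25 | 0.406 | 72% |
| 0.5 | 0.438 | 79% |
| 0.75 | 0.469 | 84% |
| 1 | 0.500 | 88% |

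Power reaches 80% once f is about 0.57.

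**The case against.** **All 160 are analysed, so nothing is lost.** This is the strongest reply, and part of it stands. Under the intention-to-treat rule the analysis set is 160. The 120 are those with observed outcomes, and 77.5% is the power of a comparison among them, not of the planned analysis. But the rule does not repair the sentence. If carrying values forward cost nothing, there would be no dropout to compensate for. Whether 80% is reached depends on f: participants who leave after the immediate post-test may keep most of the effect, while those with only a pre-test score keep none. The article gives no value.

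**The shortfall is small and conditional.** This stands. It is 8 subjects and about 2.5 power points, or 1.8 points below 80% by the normal approximation, and it arises only if loss exceeds 20%. The article also does not say whether the 25% refers to the immediate or the 6-month assessment, so power need not be short at both. A reader might infer that the trial is seriously underpowered or that its conclusions are at risk; the figures do not support that.

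**The abstract.** A reader might take 64 per arm in the abstract as a second, conflicting sample size. It matches the required number in the main text and can be read as a condensed target that leaves out the dropout margin. It merits clarification but adds nothing to the power argument.

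**Adjustment for the pre-test would recover the power.** A reader might infer this because a pre-test is collected. At 60 observed per group it would need a pre/post correlation of at least about 0.25. The article gives no correlation and plans an unadjusted t test, so this can be offered only as an assumption.

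**Conclusion.** The concern holds as a minor arithmetic error, wrong as written. The required 128 is right; the step from 128 to 160 is not. Enrolling 160 offsets 20% dropout. At the article's own 25%, 120 subjects (60 per group) have observed outcomes, and power for a 0.5 SD difference among them is 77.5%. That figure assumes that dropouts are lost, that loss is equal in the two groups, and that the target is a 0.5 SD difference. For the planned analysis of all 160, power is about 65% to 88% under the assumptions of step 5. The supportable statement is that 80% is not assured, not that it is certainly missed.

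**What to change.** Keep 160 and the 25% expectation, and let the sentence state what follows from them. Suggested text:

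> 160 subjects will be enrolled (80 per group). With 25% dropout, about 120 (60 per group) will have observed outcomes, giving about 77.5% power for a 0.5 SD difference among those observed; 80% power is kept for dropout up to 20%.

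The words on those observed keep the sentence consistent with the rule that all randomised participants are analysed. Simply relabelling the allowance as 20% is not advised: nothing in the article supports 20% as the expected loss, and it would change an expectation to fit a multiplication.

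In the abstract, state that 80 per group will be randomised. If the authors wish to say that pre-test adjustment recovers 80% power, they should label it as assuming a pre/post correlation of at least about 0.25.

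The cost is one rewritten sentence, one number in the abstract and a slightly less favourable power figure. No extra subjects are needed. If 80% power at 25% loss is preferred, the price is 86 per group, 12 more subjects than planned.

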### Ethical Considerations

Participation will be anonymous and voluntary, and all subjects will be asked to provide written informed consent, according to Brazilian Health Ministry´s regulations (Multimedia Appendix 1). The study protocol was approved by our local Research Ethics Committee (UEL, #051/2011 and #051/2012), and registered by UEL research board (Research Project #07471).

## Results

InsuOnline is currently at the final stages of development and programming of its alpha version. The research team is currently playing and testing this version of the software, in order to detect and correct occasional bugs or problems.

The adventure genre was chosen, since it allows the learner to explore and try to solve consecutive problems, a design most compatible with adult education principles [11]. The game is represented in 3D, with third-person vision, representing the behavior of the character at scene. The characters were designed to present a visual appearance that slightly resembles those in the classic game "The Sims" [37], in that they were not too serious/realistic or cartoon-like. A few screenshots of the game can be seen in the Figures 2 to 5.

The programming was done using the game engine Unity, and the 3D-Suite Blender was used for the character modeling and animation. Players´ interaction with the game is made via mouse.

**Figure 2 figure2:**
[figure not shown]
The main characters: the young doctor (player´s avatar), the nurse, and the older doctor (mentor).

**Figure 3 figure3:**
[figure not shown]
InsuOnline main menu.

**Figure 4 figure4:**
[figure not shown]
Panel for insulin prescription.

**Figure 5 figure5:**
[figure not shown]
Feedback from the mentor after a player´s action.

## Discussion

Games and simulators are useful for health care professionals´ education on various fields [38]. Specifically regarding diabetes education, a few simulators are available for clinicians to learn and practice insulin prescribing. These have been well accepted by the target audience, but lack an objective measurement of their educational efficacy [22-25]. However in our opinion, these tools have few ways of interaction and are excessively text-based. As a result, the existing simulators are not very attractive and probably unsuccessful for arousing the intrinsic motivation of their audience, who will often need some external stimuli in order to play them.

In order to fulfill learning purposes, any intervention must incorporate the main principles of adult education**:** individualized, self-pacing, contextualized learning, with active experimentation and appreciation of previous knowledge [12,27,39]. The inclusion of game elements adds entertainment to the learning experience, increasing the intrinsical motivation of the learner to practice and to learn, making the learning experience more enjoyable and potentially more effective [39]. For these reasons, games can be a more interesting and successful approach to CME than simulators and other forms of distance education, such as virtual world interventions [40] or telemedicine consultations [41].

Many games have been developed for education of diabetic patients showing good results, including reducing the rates of urgent hospitalization of diabetic children, for example [42]. However to our knowledge, there were no reported games for education of medical doctors on insulin or DM, and this is the first report of a game oriented to education of primary care physicians on insulin prescription (initiation, adjustment, and problem solving). The need of a new approach for education of health professionals regarding insulin therapy is justified by their difficulties in this field. In Londrina, 87% of PCPs directly involved in the treatment of diabetic patients reported at least one difficulty or insecurity with insulin use, and 38% admitted that they would not initiate insulin for a hypothetical patient with type 2 diabetes who was clearly in need of insulin initiation [43].

Also, this is the first known research trial studying the educational efficacy of a computer game in teaching PCPs about insulin therapy for DM. This is important, as most games for health care have not been validated as tools for education or health outcomes improvement, and there is a great need of good quality studies which can provide good scientific evidences to support the fast-growing field of games for health. Therefore, our study was designed to follow the rigorous guidelines for research on games´ effectiveness proposed by Kato [44].

We hope to demonstrate that a game can be an attractive and effective option for CME on insulin and diabetes. If we can do that, it would give more support to the idea that games can be very good options for large-scale CME, since they can be published on the Web to reach more health professionals compared to traditional learning activities, such as conferences or symposia, which cost substantial amount of time and money. A well-designed Web-based learning game can be used by the learners in their own time and rhythm, at possibly smaller costs, and have a number of significant potential advantages.

In conclusion, we demonstrated that the design and development of a game for education of PCPs on insulin management is possible with the collaboration of a multidisciplinary team. Although its efficacy still needs further evaluation, we think that InsuOnline can be a valuable tool for large-scale CME on DM, in view of its easy dissemination on the Web, customizable content, and accordance with adult learning principles. We hope it can contribute to improving PCPs´ knowledge and optimize DM control in primary care.

## Abbreviations

A1c: glycated hemoglobin A1c
BMI: body mass index
CME: continuing medical education
DM: diabetes mellitus
PCP: primary care physicians
UEL: Universidade Estadual de Londrina
